### Randomization

2.5.

Participants will be equally (1:1) and randomly assigned to one of the two between-subjects conditions (intervention group receiving dCBT-I vs. control group filling in a sleep diary every day) while paying attention to matching both groups in age and gender. Study conductors cannot be blind due to practical reasons of study implementation.

### Treatments/interventions

2.6.

Since the intervention is planned as an add-on intervention, all participants will receive TAU in the clinic they are recruited from and are free to use any form of treatment that is offered to them. Due to the multicentre approach, TAU may differ between participants and will be recorded at T1 after the sleep intervention is completed. Potentially different therapeutic approaches in TAU will be included in exploratory data analysis.

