### Trial design

2.1.

The planned study is designed as a randomized between-subjects trial with two active groups (one intervention group receiving app-based CBT-I for approximately 8 weeks and one filling in a sleep diary for the same time span). The study intervention functions as an add-on intervention so both groups will receive TAU while undergoing study intervention. Therapists at the study centers delivering the TAU interventions will be blind towards study arm allocation of participants.

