### Procedure and assessment

2.7.

After the recruitment procedure is completed, participants will provide written informed consent and are randomized to one of the two study conditions. Participants will then receive a link to an online questionnaire arranged in SoSciSurvey for baseline assessment (timepoint T0). Following baseline assessment, the intervention group will get access to the *somnio* app and receive dCBT-I for the subsequent 8 weeks whereas the control group will fill in an online sleep diary every day (link provided by email). Five weeks after the start of the intervention, participants will receive a phone call to encourage compliance and spot potential issues with the use of the app or sleep diary. Both groups will continue to participate in TAU of the respective clinic without any limitations. After the intervention phase (10 weeks post baseline), all participants will receive a link to a second online assessment (timepoint T1). Additionally, the researchers conducting the study will contact every participant for a phone interview around T1 to gather information about current medication, number, and content of trauma-related outpatient treatment sessions. Six months after baseline assessment, participants will be contacted again and asked to fill in a follow-up assessment (T2). All measures used for the assessments on different time points are listed in Table 2. At all assessments, participants have the possibility to pause filling out the questionnaires in case they become overwhelmed and are allowed to resume at a later point during assessment day.

**Table 2. T0002:** Measures used for the assessments on different time points.

	Pre-intervention	Post-intervention	
	T0	T1	T2
Demographic data	x		
Sleep diary	x	x	x
MCTQ	x		
PSQI	x	x	x
LEC-5	x		
PCL-5	x	x	x
PCTI	x	x	x
CTQ	x		
BDI-II	x	x	x
BAI	x	x	x
WHODAS 2.0	x	x	x

Abbreviations: *BAI*, Beck Anxiety Inventory; *BDI-II*, Beck-Depressions-Inventar; *CTQ*, Child Trauma Questionnaire; *LEC-5*, Life Events Checklist for DSM-5; *MCTQ*, Munich ChronoType Questionnaire; *PCL-5*, PTSD Checklist for DSM-5; *PCTI*, Post-traumatic Cognitions Inventory; *PSQI*, Pittsburgh Sleep Quality Index; *WHODAS 2.0*, WHO Disability Assessment Schedule.

x, Instrument is assessed at respective timepoint.

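### Background treatment is recorded only around T1, so care in weeks 10 to 26 before the T2 PTSD outcomes has no stated record and the T2 result will be hard to interpret

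*Protocol article*

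**What the plan says.** All references are to the protocol article.

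- **Freedom of treatment.** Under section 2.6, participants in both arms "are free to use any form of treatment that is offered to them".
- **When it is recorded.** The same section states that "TAU may differ between participants and will be recorded at T1 after the sleep intervention is completed".
- **How it is recorded.** Section 2.7 says the researchers will "contact every participant for a phone interview around T1 to gather information about current medication, number, and content of trauma-related outpatient treatment sessions".
- **Timing of T1.** "After the intervention phase (10 weeks post baseline), all participants will receive a link to a second online assessment (timepoint T1").
- **Timing of T2.** "Six months after baseline assessment, participants will be contacted again and asked to fill in a follow-up assessment (T2"). No treatment interview or treatment item is described there.
- **Use of the record.** Section 2.9 fits a model over T0, T1 and T2. It classifies sessions as trauma-focused or not, asks whether therapy included a sleep intervention, and enters treatment content as a covariate and in exploratory analyses. The stated aim is to control for the main confounding from differences in treatment.
- **Outcomes.** Section 2.8.1 makes PTSD severity and probable PTSD on the PCL-5 primary. Section 2.7 collects the PCL-5 at T0, T1 and T2.
- **Blinding.** "Study conductors cannot be blind due to practical reasons of study implementation" (section 2.5), whereas section 2.1 states that "Therapists at the study centers delivering the TAU interventions will be blind towards study arm allocation of participants".

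**The concern.** The protocol treats variation in usual treatment as important enough to classify and adjust for, and the Discussion hopes to learn which other interventions combine well with CBT-I. Yet the only stated record closes around week 10, while a primary time point lies at six months. Someone whose therapy was not trauma-focused by week 10 but became so afterwards would carry the wrong label into the T2 analysis.

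Care that begins after T1 may also differ by arm. Participants who are still unwell at T1 may start other therapy or medication. Section 2.6.1 notes that doctors and psychologists can prescribe the study app, so a control participant could obtain it outside the study before T2. Nothing in the plan would show this. A null T2 result could then mean that the app has no lasting effect or that the control arm caught up through other care. A positive result could likewise include extra care in the app arm.

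There is a smaller gap within the first ten weeks. The medication question concerns what is being taken at the time of the call, so a drug started and stopped earlier is missed. No general medication record at baseline is described, so a new drug cannot be told from a long-standing one.

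**Working it through.** **1. Coverage of the treatment record.** Inputs: T1 at 10 weeks and T2 at six months (section 2.7). Six months is taken as 26 weeks, which is an assumption of calendar length only.

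- Covered by the T1 interview: 10/26 = 38%.
- Not covered by any stated record: 26 − 10 = 16 weeks; 16/26 = 62%.

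These are shares of calendar time. The article does not say how much treatment falls after week 10.

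**2. The plan's own scale.** The article gives no figure for treatment after T1. The nearest yardstick is the planning effect in section 2.4, Cohen's *f* = 0.25, which for two equal groups is *d* = 2 × 0.25 = 0.5. The stated *N* = 86 reproduces as a between-group test over three time points (noncentral *F*, α = 5%, power 0.8015) if a correlation of 0.5 between time points is assumed, since the article gives none. That is 43 per arm. This point disputes no sample-size figure.

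**3. How far later care could move the T2 difference.** If later treatment is worth *D* standard deviations and its uptake between T1 and T2 differs by *p* between arms, the T2 difference shifts by *D* × *p*. Both inputs are assumptions, not document figures.

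| *D* (SD) | *p* = 5 points | 10 points | 20 points | 30 points |
|---|---|---|---|---|
| 0.3 | 0.015 | 0.03 | 0.06 | 0.09 |
| 0.5 | 0.025 | 0.05 | 0.10 | 0.15 |
| 0.8 | 0.04 | 0.08 | 0.16 | 0.24 |
| 1.0 | 0.05 | 0.10 | 0.20 | 0.30 |

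Against *d* = 0.5 the range is 0.015/0.5 = 3% to 0.30/0.5 = 60%. The shift can go either way, depending on which arm seeks more care.

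**4. What part of this is chance.** With 43 per arm and 50% uptake, the standard deviation of the uptake difference from randomisation alone is √(2 × 0.25/43) = 0.11. An imbalance of that order is already part of the random error of the comparison. Only a systematic difference by arm matters here, and that would itself be a consequence of allocation.

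**5. Stated aim against stated data.** Section 2.9 uses treatment content in a model that includes T2. Sections 2.6 and 2.7 supply that content up to about week 10 only. For T1 the label and the outcome cover the same period. For T2 they do not.

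**The case against.** A reader might infer that the six-month difference cannot be attributed to the app at all. The documents do not support that. Allocation is randomised 1:1 (section 2.5) and an intention-to-treat analysis is planned (section 2.9). The T2 contrast therefore estimates the effect of offering the app rather than the diary on top of whatever care follows, whether or not that care is recorded. Treatment begun after randomisation is a possible consequence of arm, not a baseline confounder. The Discussion openly chooses this real-world question and relies on randomisation as well as assessment. This objection stands and limits the point to interpretation.

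Other stronger readings also fail:

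- **That treatment behind T2 is wholly unmeasured.** The first ten weeks lie behind T2 as well, and they are recorded. For medication, benzodiazepines and benzodiazepine receptor agonists are an exclusion criterion at entry (section 2.3), and the Discussion excepts benzodiazepines from the additional help allowed.
- **That Table 2 proves the gap.** Table 2 has no treatment row even at T1, where the text says treatment is recorded, and it omits the insomnia severity index named in section 2.8.2. The point rests on the explicit wording of sections 2.6 and 2.7.
- **That the T1 record is biased by arm because unblinded staff collect it.** The interviewers can be taken to know the arm, but patient recall is inferred from the use of a phone call, and no mechanism or size of bias is given. Blinding of the therapists also limits unequal provision by arm, although not care that participants seek for themselves.

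It can also be said that a condensed article may leave treatment forms to the full protocol. Here, however, the article itself says when, how and by whom treatment is recorded, and names T1 only.

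**Conclusion.** The point holds as a gap in data collection that limits what can be concluded at T2. It does not undermine the randomised comparison. About 16 of the 26 weeks before T2 have no stated treatment or medication record. The trauma-focused and sleep-intervention labels may therefore misdescribe treatment behind the T2 outcomes, and the aim in section 2.9 of controlling treatment differences is only partly met there. Co-treatment or contamination that differs by arm after T1 cannot be seen.

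The documents do not allow the size of any such difference to be bounded. The 3% to 60% of the planning effect shown above depends wholly on assumed values and indicates scale only. The coverage figure rests on reading six months as 26 weeks and on taking the article's description of the record as complete.

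A related caution follows from section 2.9. Adjusting the main contrast for treatment received after randomisation can itself introduce bias, and a fuller record would not cure that. The value of the added data is description and exploratory analysis.

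**What to change.** 1. Add the same short usual-treatment and medication items to the existing T2 online questionnaire, covering the period since T1. Include sleep treatments and use of the app outside the study.
2. Add a brief medication item to the T0 questionnaire.
3. At T1, ask about all medication since baseline, not only what is being taken at the time of the call.
4. Report treatment and medication by arm, separately for T0–T1 and T1–T2, as description.
5. State that treatment received after randomisation will not be used to adjust the main T2 contrast, and keep it for exploratory analyses.

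The cost is slightly longer questionnaires at T0 and T2 and a wider question in a call that is already planned. No extra visit or staff is needed. Taking session content from a therapist form would be an optional extra and is not required to close the gap.

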#### Intervention group

2.6.1.

Participants in the intervention group will get access to the sleep app *somnio* which serves as the form of dCBT-I employed in this study. *Somnio* is the first digital health application listed permanently with the German Federal Institute for Drugs and Medical Devices for the treatment of insomnia and therefore approved for prescription by medical doctors and psychologists since 2020 (mementor DE GmbH, Leipzig, Deutschland). It belongs to the best rated dCBT-I (Simon et al., 2023) and has been shown to significantly and long-lastingly improve insomnia (Lorenz et al., 2019; Maurer et al., 2023), as well as epiphenomena such as daytime functioning, quality of life, symptoms of depression and anxiety (Schuffelen et al., 2023). Compliance data and completion rates of 68% are promising as well for *somnio*, even in a heterogeneous real-world sample (Schuffelen et al., 2023) which is indeed slightly lower than some reported compliance rates for CBT-I that is delivered in person. However, with 48–91% there is also a wide range of compliance rates in this intervention type (Mellor et al., 2022) and *somnio*'s data fall completely within that range. One activation code is valid for 90 days and users can access the application via app or web browser. The intervention period for this respective study is planned for approximately 8 weeks. The intervention program consists of 10 educative core- and 6 concomitant-modules which are based on Morins microanalytic model of insomnia (Morin, 1993a). In this model, it is stated that insomnia is primarily sustained by a cycle of self-perpetuating factors such as high arousal, negative consequences, maladaptive habits and dysfunctional cognitions about sleep (Perlis et al., 2005). Users are guided through the intervention program by an animated sleep coach called Albert to create a tailored dialogue that is based on pre-programmed input by CBT-I experienced psychotherapists. A list and description of all educative modules and the closing session can be found in Table 1.

**Table 1. T0001:** Content of dCBT-I application somnio.

Module	Content description
Introduction	Introduction to therapy content and procedure, personalization of settings, recording of sleep symptoms and therapy goals
Sleep diary	Introduction to sleep diary as basis for subsequent personalized training and instructions on how to fill in the reports
Sleep knowledge	Psychoeducation on sleep phases, 2-process model of sleep (sleep pressure and circadian rhythm) and individual differences concerning sleep and chronotypes
Practical exercise	Deepening of sleep-related knowledge using practical exercises (taking the role of a sleep expert who gives advice to a patient suffering from insomnia similar to the user's symptoms)
Cycle of insomnia	Introduction to cycle of insomnia according to cognitive model of insomnia (Morin, 1993a) including dysfunctional sleep behaviours, hyperarousal, dysfunctional cognitions, and consequences; creation of individual insomnia model
Sleeping hours	Sleep time, introduction of sleep restriction and definition of individual sleep window (based on individual mean sleep duration within the last 7 days reported in the sleep diary)
Relaxation	Relaxation, introduction of progressive muscle relaxation and instruction to practice further with a provided audio file (aim of reducing physical and mental tension to enhance sleep onset latency and waking after sleep onset)
Sleep behaviour	Sleep behaviour, improvement of dysfunctional sleep habits (sleep hygiene) and introduction of stimulus control principle
Thoughts	Sleep-related cognitions, introduction of connection between emotions and cognitions and consequences of dysfunctional sleep-related cognitions; instruction to identify and dispute dysfunctional sleep-related cognitions
Everyday decisions	Integration of therapy content into everyday decisions by presenting different scenarios for which the user has to decide on how to behave
Closing session	Brief repetition of therapy content and quiz, reflection on goals and achievements, planning of time succeeding the intervention program

Note. dCBT-I, digital cognitive-behavioural therapy for insomnia.

#### Control group

2.6.2.

The control group will be asked to fill in a sleep diary in online format (link will be sent by email everyday) for 8 weeks which is the same time span as the *somnio* app is processed by the intervention group. For ethical reasons, we intend to offer a *somnio* app activation code to participants of the control group after study completion, too.

### Procedure and assessment

2.7.

After the recruitment procedure is completed, participants will provide written informed consent and are randomized to one of the two study conditions. Participants will then receive a link to an online questionnaire arranged in SoSciSurvey for baseline assessment (timepoint T0). Following baseline assessment, the intervention group will get access to the *somnio* app and receive dCBT-I for the subsequent 8 weeks whereas the control group will fill in an online sleep diary every day (link provided by email). Five weeks after the start of the intervention, participants will receive a phone call to encourage compliance and spot potential issues with the use of the app or sleep diary. Both groups will continue to participate in TAU of the respective clinic without any limitations. After the intervention phase (10 weeks post baseline), all participants will receive a link to a second online assessment (timepoint T1). Additionally, the researchers conducting the study will contact every participant for a phone interview around T1 to gather information about current medication, number, and content of trauma-related outpatient treatment sessions. Six months after baseline assessment, participants will be contacted again and asked to fill in a follow-up assessment (T2). All measures used for the assessments on different time points are listed in Table 2. At all assessments, participants have the possibility to pause filling out the questionnaires in case they become overwhelmed and are allowed to resume at a later point during assessment day.

**Table 2. T0002:** Measures used for the assessments on different time points.

	Pre-intervention	Post-intervention	
	T0	T1	T2
Demographic data	x		
Sleep diary	x	x	x
MCTQ	x		
PSQI	x	x	x
LEC-5	x		
PCL-5	x	x	x
PCTI	x	x	x
CTQ	x		
BDI-II	x	x	x
BAI	x	x	x
WHODAS 2.0	x	x	x

Abbreviations: *BAI*, Beck Anxiety Inventory; *BDI-II*, Beck-Depressions-Inventar; *CTQ*, Child Trauma Questionnaire; *LEC-5*, Life Events Checklist for DSM-5; *MCTQ*, Munich ChronoType Questionnaire; *PCL-5*, PTSD Checklist for DSM-5; *PCTI*, Post-traumatic Cognitions Inventory; *PSQI*, Pittsburgh Sleep Quality Index; *WHODAS 2.0*, WHO Disability Assessment Schedule.

x, Instrument is assessed at respective timepoint.

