### Participants

2.3.

Participants aged between 18 and 55 years will be included in the study if they (1) have experienced a traumatic event within the past three months as measured with Life Events Checklist (LEC-5; Weathers et al., 2013) and show PTSD symptoms (PTSD Checklist for DSM-5 (PCL-5) score above cut-off value of 33) and (2) report on sleep disturbances which evolved or became stronger after the traumatic experience. Participants will be excluded from the study if they (1) take benzodiazepines or benzodiazepine receptor agonists, (2) report on a lifetime diagnosis of psychosis, bipolar disorder or more than two episodes of major depression, (3) have suffered from an alcohol or substance use disorder within the past year, (4) have an IQ < than 80 points, (5) are diagnosed with any systemic or neurological disorder (e.g. dementia), (6) show signs of acute suicidality, (7) are insufficiently able to communicate in German, (8) work in shifts or have had an intercontinental flight crossing two or more time zones within the past 30 days or (9) suffer from sleep apnea.

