#### Primary outcome measures

2.8.1.

The primary outcome measures are PTSD symptom severity and number of participants with probable PTSD according to a PCL-5 cut-off of 33, which showed the best sensitivity-to-specificity-ratio for detecting PTSD (Weathers et al., 2013). Due to the online-design, we could not use CAPS interview as Pigeon et al. (2022) did to survey PTSD symptom development and decided to use PTSD Checklist for DSM-5 (PCL-5; Weathers et al., 2013) and Post-traumatic Cognitions Inventory (PCTI; Foa et al., 1999) as self-reports instead, both applied at T0, T1 and T2. Whereas the PCL-5 covers all PTSD symptoms, PTCI specifically measures trauma-related cognitions. The PCL-5 asks respondents to rate bothering of PTSD symptoms during the past month on a 5-point likert scale (1 = not at all to 5 = extremely) and has strong internal consistency (*α* = .94), test–retest reliability (*r* = .82), and convergent (*rs* = .74 to .85) and discriminant (*rs* = .31 to .60) validity (Blevins et al., 2015). The PTCI consists of 33 questions about trauma-related cognitions (based on the three factors Negative Cognitions About Self, Negative Cognitions About the World and Self-blame) which respondents rate on a 7-point-likert scale (absolutely no consent to strong consent). As PCL-5, PTCI shows excellent psychometric properties with internal consistency ranging from *α* = of .86–.97 (Foa et al., 1999). As the PCL-5 contains the item ‘Trouble falling or staying asleep?’ (Weathers et al., 2013), all analyses for the PCL-5 will be conducted with and without this item separately to detect whether potential changes on this measurement are solely driven by changes in sleep quality.

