### Statistical analysis

2.9.

Statistical analyses will be based on a mixed general linear model design with the two-level between group factor intervention (intervention vs. control group) and the three-level within group factor time (assessments at T0, T1 and T2) for primary and secondary outcome measures to account for both hypotheses tested in this study. A multilevel approach including study centers with their, presumably, differing TAU interventions, is not feasible due to too low a number of study centers at this hierarchical level. However, as discussed below, study centre and TAU interventions will be used as covariates and for exploratory analyses. For the first research question, the interaction between groups and time will be analysed to determine whether PTSD symptom severity differs for the intervention group after receiving the add-on treatment. For the second research questions, sleep disturbance before the intervention will be used to predict PTSD symptom severity at first and second follow-up for both groups. Due to the exploratory nature of this study, analysis will be conducted both with an intention-to-treat and a per-protocol approach, allowing for a comparison of both effect estimates (Gupta, 2011). For intention-to-treat analysis, dropouts will be included with a last observation carried forward strategy. Extreme cases and outliers will be checked for validity and excluded for per-protocol analysis if indicated. Dropouts will be reported with time point and reason in the final results. We intend to include age, gender, severity of trauma (indicated by classification in type-1 and -2 traumata), number of previous traumatic events, content of trauma-related outpatient treatment sessions and recruiting centre as covariates and in further exploratory analyses. Despite our efforts to proactively reduce variance in trauma treatment among participating trauma centers by organizing joint supervisions, we assume there will be left some significant variance that has to be considered in the statistical analyses. The content of trauma-related outpatient treatment sessions will be classified into trauma-focused versus non-trauma-focused therapy elements since it has been shown that in symptomatic acutely traumatized individuals this may cause a significant difference in treatment outcome (Roberts et al., 2019). Furthermore, we will survey whether sleep interventions have been included in the therapy process or not. By this, we intend to control for the most relevant confounding factors arising from between-participant-treatment-differences.

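### Randomization comes before the T0 questionnaire, and nothing says allocation is withheld until T0 is returned, so the baseline PCL-5 may be reported with knowledge of arm or be missing

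*Protocol article*

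**What the plan says.** Section 2.7 (Procedure and assessment) gives the order. After recruitment is complete, participants consent, then "are randomized to one of the two study conditions. Participants will then receive a link to an online questionnaire", which is the T0 baseline. Treatment starts later: "Following baseline assessment, the intervention group will get access to the" app, while the control group begins its daily diary.

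On blinding, section 2.5 (Randomization) says "Study conductors cannot be blind due to practical reasons of study implementation". Section 2.1 (Trial design) says "Therapists at the study centers delivering the TAU interventions will be blind towards study arm allocation of participants". Nothing is said about when participants are told their arm.

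On the outcome, section 2.8.1 uses the PCL-5 and the PTCI "as self-reports instead, both applied at T0, T1 and T2". Section 2.9 (Statistical analysis) has a "three-level within group factor time (assessments at T0, T1 and T2"), and says "For the first research question, the interaction between groups and time will be analysed". The intention-to-treat analysis brings dropouts in by last observation carried forward.

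Section 2.8.2 places the baseline sleep-diary entries in the week before the intervention, so baseline collection extends over about a week.

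**The concern.** In most trials a baseline collected after randomization is a modest weakness. Three features make it matter more here.

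- The primary outcome is self-reported, so no blinded assessor stands between knowledge of arm and the score.
- T0 is part of the outcome vector in the tested interaction. It is not merely a descriptive baseline.
- The two conditions, a therapy app and a daily diary, are easy to tell apart once named, and the staff who know the allocation are the staff running the study.

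If participants know their arm when they answer T0, hope in one group or disappointment in the other could move the baseline by arm. That shift would be read as change over time. The T0 sleep measures, which are the predictors for the second research question, are collected at the same point.

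The second issue does not depend on blinding. Between randomization and T0 a person can be lost with no T0 score on file. Last observation carried forward, as described, cannot place that person in the analysis. The Discussion relies on intention-to-treat and on comparing dropout characteristics to deal with selective loss, but most characteristics are first scheduled at T0.

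**Working it through.** **1. Order of events.** Reading 2.7 with 2.2: screening interview and final inclusion; consent; randomization; T0 link; T0 returned; app or diary released. The gap of interest lies between randomization and the return of T0.

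**2. The plan's own sample size, as a check on the model.** Inputs from 2.4: f = 0.25, power 80%, alpha 5%, a between-factor effect in a mixed design. From 2.9: two groups, m = 3 time points. The correlation between time points is not given, so rho = 0.5 is assumed.

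- Noncentrality = f² × N × m / (1 + (m − 1) × rho) = 0.0625 × 86 × 3 / 2 = 8.06, with df 1 and 84.
- Power at N = 86 is 0.801; at N = 84 it is 0.792. The stated N = 86 is reproduced.

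The present point does not depend on this figure, and changing the order would not alter it.

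**3. Effect of a T0 shift on a change contrast.** Let one arm's T0 mean move by k, with T1 and T2 unaffected. The between-arm difference in T1 − T0 then moves by exactly k, as does that in T2 − T0. For two equal groups d = 2f = 0.5. For an assumed k of 0.2 SD, 0.2 / 0.5 = 40% of the planned effect.

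**4. Effect on the interaction test.** Assume no true effect, a between-arm difference of k (in SD) at T0 only, and sphericity. Centring (k, 0, 0) over time and splitting it equally between arms gives a sum of squares of k²/6, so

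- noncentrality = N × k² / (6 × (1 − rho)), with df 2 and 2(N − 2).
- For N = 86, k = 0.2, rho = 0.5: 86 × 0.04 / (6 × 0.5) = 1.15.

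Rejection rates at a nominal 5%, N = 86:

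| Assumed T0 shift | rho = 0.5 | rho = 0.7 |
|---|---|---|
| 0 | 5% | 5% |
| 0.1 SD | 7% | 9% |
| 0.2 SD | 14% | 21% |
| 0.3 SD | 28% | 44% |

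At N = 104 a 0.2 SD shift gives 17% (rho = 0.5) or 25% (rho = 0.7).

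**5. Direction.** Lower PCL-5 is better. A raised T0 in the app arm would inflate the apparent benefit; a raised T0 in the control arm would hide some of it. The article gives no basis for choosing between these.

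**6. Missing T0.** Non-return rates are not given. If 2%, 5% or 10% of 104 never returned T0 (assumed), 104 × 0.02 = 2.1, 104 × 0.05 = 5.2 and 104 × 0.10 = 10.4, that is about 2, 5 or 10 randomized people with no T0 value.

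**The case against.** The strongest reply is that nothing in the article says participants know their arm at T0. App access and the control diary both follow T0, so the visible signs of allocation come later, and treatment itself cannot affect the T0 answers. The statement on unblinded staff concerns the study conductors, and T0 is an online form. The moment of disclosure may be fixed in a fuller document. This stands in part. A reader might infer that participants are known to be unblinded at T0; the article does not support that. It supports only that they may be, because the stated order allows it and no safeguard is described. The order itself is stated outright and is not a detail left out by condensing.

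A reader might also infer from Table 2, which lists the LEC-5 only at T0, that eligibility is tested after randomization. It is not. Section 2.2 has a screening interview that checks all criteria before final inclusion. Section 2.3 requires "a traumatic event within the past three months as measured with Life Events Checklist" and a PCL-5 above the cut-off as inclusion criteria. Table 2 covers T0 to T2 and does not list screening.

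It can further be said that the article never defines the intention-to-treat set as those with T0, that 20% attrition is already allowed for, and that a PCL-5 from before randomization should exist for everyone included. All true. So a reader should not conclude that people without T0 are declared excluded. But the screening score is not named as baseline or fallback, and the one imputation rule given does not cover the case.

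Finally, the shift sizes and non-return rates are assumptions, and no reordering removes expectancy from self-reports at T1 and T2. That is correct, and it limits the claim to the baseline.

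**Conclusion.** The point holds in a limited form. The protocol article randomizes before T0 and describes nothing that withholds allocation until T0 is returned. The self-reported baseline, a level of the primary interaction test, may therefore be given with knowledge of arm, and may be absent for some randomized people in a way that last observation carried forward cannot repair.

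Whether a shift occurs, how large it would be and which arm it would favour are unknown. The illustrations (0.2 SD as 40% of d = 0.5; a false-positive rate of about 7% to 28% for shifts of 0.1 to 0.3 SD at correlation 0.5, or 9% to 44% at 0.7) rest on assumed shifts and correlations, sphericity and N = 86. They show how sensitive the test is to a T0 shift and are not estimates of actual bias. The point is worth acting on because the remedy is cheap and removes both problems at the baseline.

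**What to change.** Change the order in 2.7 to: consent; T0 questionnaire and baseline sleep-diary week; randomization once these are submitted; then release of the app code or diary link. T0 is already an online form completed before release, so no visit or staff time is added. The cost is that randomization waits for T0, and people who do not return it are not randomized.

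If the order must stay, add two statements:

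- Allocation is disclosed to participants only after T0 has been submitted.
- For randomized people without T0, the PCL-5 from the pre-randomization screening serves as baseline, and the number of such people is reported by arm.

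The second option is weaker. It depends on unblinded staff keeping the allocation from participants for the length of the baseline period, and it mixes two baseline sources. The screening score was also subject to the eligibility cut-off.
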